### Data analysis

All analyses will be conducted on an intention to treat basis, including all randomised young people in the groups to which their year group was allocated irrespective of deviations based on non-compliance, unless otherwise stated. Data from the internal pilot will be used in all analyses.

The primary analysis will compare the proportion of young people with any treated or untreated caries in permanent teeth at 2 and 3 years between the intervention and control groups using a repeated measures binary logistic multilevel model, with the primary time-point of interest at 3 years. The model will control for presence or absence of caries at baseline, year group, time and an interaction between treatment and time as fixed effect covariates. Pupils and school will be included as random effects (to allow for clustering of data within each pupil (over time) and school). Cohen’s kappa coefficient will be used to measure the intra-examiner agreement of presence of carious lesions at ICDAS code 4–6 for 5% of participants who will be examined twice at a particular time point.

A subgroup analysis will be conducted looking at participants with baseline caries by including presence or absence of caries at baseline in an interaction with treatment group in the primary model. The hypothesis is that young people with caries at baseline are more likely to have caries at follow-up than those who do not have caries at baseline.

Secondary analyses will compare self-reported twice-daily brushing frequency at 6 months and 1, 2 and 3 years using a repeated measures binary logistic multilevel model. Continuous measures (Plaque Index Gingival Index of Löe), mean number of bleeding gingival sites per child and CARIES-QC will be analysed using a covariance pattern model. Other secondary outcomes will be analysed using appropriate regression techniques.

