### Outcome measures

#### Primary outcome

The primary outcome for this trial is the presence of at least one treated or untreated carious lesion in any permanent tooth measured at the young person-level using the permanent tooth index 'DMFT' (Decayed, Missing and Filled Teeth) where decay is measured as carious lesions extending into dentine - International Caries Detection and Assessment System (ICDAS) levels 4-6 [33], at three years follow-up. The outcome will be measured cross-sectionally at 3 years, and is regardless of the presence or absence of caries in the teeth at baseline.

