##### Sample size

The estimated proportion of UK 12 year olds with caries is 32%, with estimates of 46% for those eligible for FSM and 30% for those not eligible for FSM [4, 40]. Based on a systematic review of interventions for caries prevention to increase the frequency of toothbrushing [41], an absolute reduction in the proportion of young people with caries of 8% might be expected with this intervention. An individually randomised trial powered at 90% (5% two-sided α) to detect a reduction in the proportion of young people with caries from 32% to 24% would require a sample size of 1320. Since this is a cluster trial, this figure needs to be inflated to account for the correlation of the outcomes within schools, as measured by the intraclass correlation coefficient (ICC). Few estimates of a school-level ICC are available for dental data. In a previous study evaluating a behaviour change programme for preventing dental caries in primary schools, an ICC of 0.01 was used, which was estimated using their own unpublished data [42]; a more conservative ICC of 0.02 has been chosen for this trial.

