Additionally, since randomisation is taking place at the level of the year group, and not at the school-level, there is the potential for some contamination (e.g. pupils in the year group assigned to the control arm receiving information about the intervention from pupils in the other participating year group assigned to receive the intervention). There is an argument to therefore increase the sample size further to account for some level of contamination, which has the potential to dilute the treatment effect. We have assumed only partial contamination effects (i.e. those contaminated gain half the treatment benefits as it is unlikely that any pupil in the control group would receive all the intervention) for 27% of the control group pupils (based on findings from the internal pilot phase of the trial). In total, 40 schools are required assuming within-school (year group level randomisation), an average of 60 pupils per year group, an ICC of 0.02, and 20% pupil-level attrition at follow-up. This would give us 90% power (5% two-sided α) to detect an 8% absolute reduction, from 32% to 24%, in the proportion of pupils with caries. An attrition rate of 20% was estimated as the pupils will continue to be at school for the duration of the trial so it will be possible to reach and engage with them through the school and in an environment they recognise as educational and supporting their interests. Overall, 42 schools will be recruited to allow for the potential that a small number of schools may withdraw.

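### The primary model puts a pupil random intercept on two nearly identical caries outcomes, so the size of its odds ratio depends mainly on how often examiners reverse themselves

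*Protocol article*

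**What the plan says.** The Primary outcome section defines a yes/no endpoint per pupil: at least one lesion into dentine in a permanent tooth, treated or untreated, by the decayed, missing and filled index. It adds: "The outcome will be measured cross-sectionally at 3 years, and is regardless of the presence or absence of caries in the teeth at baseline".

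The Data analysis section says the primary analysis compares the proportions with caries at 2 and 3 years, "using a repeated measures binary logistic multilevel model, with the primary time-point of interest at 3 years". It continues: "The model will control for presence or absence of caries at baseline, year group, time and an interaction between treatment and time". Pupil and school are random effects.

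The Sample size section powers the trial "to detect an 8% absolute reduction, from 32% to 24%, in the proportion of pupils with caries". The article names no effect measure for the primary result. It states no step that turns the model's odds ratio into a difference in proportions.

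**The concern.** A filled or extracted carious tooth still counts, so the outcome hardly reverses. A pupil positive at baseline stays positive at 2 and 3 years, and a pupil positive at 2 years stays positive at 3, apart from examiner error. The model therefore sees two almost identical binary outcomes per pupil and a baseline covariate that nearly determines both.

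A random-intercept logistic model explains such agreement with a very large pupil variance and a very large baseline coefficient. What keeps them finite is mainly the few pupils whose record reverses. The treatment odds ratio is conditional on the pupil intercept, so it stretches with that variance. Two trials with the same effect on caries but different examiner consistency would report quite different primary odds ratios, and neither could be set beside the planned 32% against 24%. With very consistent examiners the fit may also depend on the integration method or fail to settle.

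**Working it through.** **1. The plan's own figures.** For 32% against 24%, 90% power, two-sided 5%, pooled variance:

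n per arm = [1.96·√(2·0.28·0.72) + 1.2816·√(0.32·0.68 + 0.24·0.76)]² / 0.08² = (1.2446 + 0.8105)² / 0.0064 = 660, total 1320. The article says the trial "would require a sample size of 1320", so this reproduces.

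Contamination (27% of controls gain half the benefit): control rate 32 − 0.27·0.5·8 = 30.92%, difference 6.92 points, 873 per arm, 1746 in total. With "an average of 60 pupils per year group, an ICC of 0.02, and 20% pupil-level attrition at follow-up": 1746 × (1 + 59·0.02) = 3806; /0.8 = 4758; /120 = 39.65, so 40 schools. This also reproduces.

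Both figures rest on a difference in proportions. The population-averaged odds ratio it implies is (0.24/0.76)/(0.32/0.68) = 0.671.

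**2. The planned model on expected data.** For pupil i at time t:

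logit P(caries) = a + b₁·treatment + b₂·time + b₃·treatment×time + b₄·baseline + uᵢ, with uᵢ ~ N(0, s²).

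The 3-year treatment odds ratio is exp(b₁ + b₃). It was fitted by maximum likelihood with fine-grid integration to expected counts for 5040 × 0.8 = 4032 pupils.

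Assumptions:
- Baseline caries 32%, with new caries of 8 points by year 2 and 12 by year 3 in controls. This gives 44% at 3 years; 32% and 44% are the Background section's figures for ages 12 and 15.
- Intervention cuts new caries by 25%, so 32 + 9 = 41% at 3 years.
- Independent examiner error at each visit, at four pupil-level sensitivity/specificity settings. The article gives none.
- School effect, year group and contamination left out.

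The comparator is a logistic model of the 3-year outcome on treatment and baseline caries, with no pupil effect.

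| Sens/spec | Pupil SD | Baseline log OR | 3-year OR, planned model | 3-year OR, comparator | Ratio of log ORs | z, planned | z, comparator |
|---|---|---|---|---|---|---|---|
| 0.99/0.995 | 8.3 | 27 | 0.26 | 0.74 | 4.5 | −2.86 | −2.99 |
| 0.97/0.99 | 5.7 | 16 | 0.43 | 0.77 | 3.2 | −2.66 | −2.75 |
| 0.95/0.98 | 4.5 | 11 | 0.56 | 0.80 | 2.6 | −2.44 | −2.49 |
| 0.90/0.97 | 3.3 | 7 | 0.69 | 0.84 | 2.1 | −2.14 | −2.15 |

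Hand check: a normal intercept stretches the log odds ratio by roughly √(1 + c·s²), with c = (16√3/(15π))² = 0.346. For s = 8.3 this is √(1 + 23.8) = 5.0; for s = 3.3 it is √(1 + 3.8) = 2.2. Both are close to the fitted ratios.

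With no error at all, no pupil goes from positive to negative and every baseline-positive pupil is positive twice. The fit then has no stable solution: the pupil SD had reached about 40 and was still rising.

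**3. Standardising the same fits.** Averaging predicted 3-year risks over the pupil effect and the baseline distribution gives differences of −2.8, −2.7, −2.7 and −2.6 points. The observed differences are −3.0, −2.9, −2.8 and −2.6.

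**4. Numerical reliability.** A second set of fits used 32% against 24% at 3 years, an assumed 28% against 21% at 2 years, 3840 pupils and no baseline covariate. With 5% of 2-year positives recorded negative at 3 years, ordinary Gauss–Hermite quadrature with 7, 15 and 25 points gave odds ratios of 2×10⁻⁸, 0.78 and 0.041, against 0.051 by accurate integration. In 25 simulated trials at 2% reversal the odds ratio ran from 0.0018 to 0.076, while the risk difference ran from 4.8 to 11.1 points.

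**The case against.** The strongest case for the plan has five parts.

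- **The test is sound.** With accurate integration the planned model's z is slightly smaller than the comparator's in every setting. This stands: the working shows no inflation of type I error.
- **The proportions can be recovered.** Step 3 comes within 0.2 points of the observed difference. This stands. A reader might infer that the model cannot deliver the difference the trial is powered on, and that is not so. The choice of reported measure may also sit in a full analysis plan.
- **A conditional odds ratio is a different quantity, not a biased one.** This stands. Part of its distance from the unadjusted odds ratio (0.89 to 0.90 in these settings) is ordinary adjustment for baseline caries, so the baseline-adjusted comparator is the fair one. Against it the log odds ratio is still about 2 to 4.5 times larger.
- **Baseline separation is not peculiar to the pupil intercept.** This stands. With no error, every baseline-positive pupil is positive in a 3-year model too, so any replacement needs a fallback.
- **The extremes need perfect examiners or crude quadrature.** This largely stands. The article plans repeat examinations with kappa, so some disagreement is expected, and all fits with examiner error converged. Adaptive quadrature would be steadier than the figures in step 4, though the estimate would stay extreme.

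The repeated-measures model also has a purpose: with 20% attrition it draws on pupils seen at 2 years but not at 3. None of this removes the dependence of the odds ratio on examiner consistency, which follows from the model the article states.

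**Conclusion.** The concern holds as a should-fix. For one fixed effect (44% against 41%), the planned model's 3-year odds ratio runs from 0.26 to 0.69 as assumed examiner accuracy falls from 0.99/0.995 to 0.90/0.97. A baseline-adjusted 3-year model without the pupil effect moves only from 0.74 to 0.84. With no examiner error the planned model has no stable solution.

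The range rests on assumed incidence, effect and error rates, and on leaving out school and year-group effects. The direction rests only on the outcome definition and the stated random effects.

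A reader might go further and infer false-positive findings or a biased treatment effect. The documents and the fits do not support that. The damage is to the size, interpretability and numerical reliability of the primary estimate.

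**What to change.** Make the primary analysis a model of the 3-year outcome alone, which matches the cross-sectional endpoint. Adjust for baseline caries and year group, allow for clustering by school and by year group within school, and drop the pupil random effect. A population-averaged (GEE) model is an equal alternative. Report the standardised risk difference with its confidence interval beside the odds ratio.

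Analyse the 2-year outcome in its own model. Bring 2-year data into the primary analysis through multiple imputation of missing 3-year outcomes. Name a penalised-likelihood fallback in case baseline caries separates.

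The cost is a change of analysis wording, with no new data. The downside is that pupils seen at 2 but not 3 years contribute only through the imputation.

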#### Secondary outcomes

Caries (D_4–6_ MFT) at 2 years: the presence of at least one treated or untreated carious lesion into dentine in permanent teeth (ICDAS levels 4–6) at 2 years follow-up.Caries (D_1–6_ MFT) at 2 and 3 years: the presence of at least one carious lesion in permanent teeth (ICDAS levels 1–6) at 2 and 3 years follow-up.Number of carious teeth at 2 and 3 years: The number of permanent teeth with any treated or untreated carious lesions (ICDAS 1-6, and caries into dentine 4-6) at 2 and 3 years.Twice-daily toothbrushing: self-reported toothbrushing frequency using validated questions from the national Child Dental Health surveys at baseline, 6 months and 1, 2 and 3 years. To validate the self-reported measure, two proxy clinical objective indicators will be collected: (i) clinically assessed plaque levels using Turesky’s modification of the Quigley Hein Plaque Index [34, 35]; and (ii) clinically assessed gingivitis using gingival bleeding (modification of the Gingival Index of Löe) [36] and mean number of bleeding gingival sites per child. The clinical measures will be carried out at baseline and at the end of years 2 and 3.

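### The primary model's only disease covariate, yes/no baseline caries, probably cannot separate the pupils still at risk; adding baseline predictors already collected would give a small gain in power at almost no cost

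*Protocol article*

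**What the plan says.** The Data analysis section specifies a repeated measures logistic multilevel model for 2 and 3 years, with pupil and school as random effects. On fixed effects it says: "The model will control for presence or absence of caries at baseline, year group, time and an interaction between treatment and time". No other baseline variable is named, and the threshold for baseline caries is not given.

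The Primary outcome section counts treated or untreated lesions at ICDAS 4–6 in any permanent tooth at 3 years, and says that the measure "is regardless of the presence or absence of caries in the teeth at baseline".

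The Secondary outcomes section lists "self-reported toothbrushing frequency using validated questions from the national Child Dental Health surveys at baseline, 6 months and 1, 2 and 3 years". Of the plaque and gingival indicators that follow, it says: "The clinical measures will be carried out at baseline and at the end of years 2 and 3". Lesions at ICDAS 1–6 appear there only as outcomes at 2 and 3 years.

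The Sample size section makes no allowance for covariate adjustment.

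**The concern.** Decayed, missing and filled teeth accumulate, so a pupil with dentine caries or a filling at baseline will almost always count as positive at 3 years whichever arm the year group is in. Nearly all information on the treatment effect comes from pupils who start negative. If the baseline term is cut at ICDAS 4–6, every one of them has the same value. Year group is then the only fixed effect describing a pupil's baseline state that still varies among them.

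The trial holds plausible predictors for exactly these pupils. Brushing is the behaviour that the intervention aims to change, and plaque and bleeding are its clinical proxies. Leaving them out of a logistic model pulls the estimated log odds ratio towards zero relative to the covariate-adjusted one and costs some power. The question is how much.

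**Working it through.** **1. The plan's own figures.** The Sample size section says "An individually randomised trial powered at 90% (5% two-sided α) to detect a reduction", and "from 32% to 24% would require a sample size of 1320". Per arm, n = [1.96√(2p̄(1−p̄)) + 1.2816√(p₁(1−p₁)+p₂(1−p₂))]² / (p₁−p₂)².

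- 32% v 24%: 659.9, so 660 per arm and 1320 in total, as stated.
- Contamination (27% of controls, where "those contaminated gain half the treatment benefits"): control rate 0.32 − 0.27 × 0.04 = 0.3092. Against 0.24 this needs 872.1, so 873 per arm and 1746 in total.
- Clustering ("a more conservative ICC of 0.02 has been chosen for this trial"): design effect 1 + 59 × 0.02 = 2.18, giving 3806.
- Attrition: 3806/0.8 = 4758. At 120 pupils per school that is 39.6, so 40 schools, as stated.
- Power with 40 schools: 4800 × 0.8/2.18/2 = 880.7 effective pupils per arm, which gives 90.3%.

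No covariate gain enters any of these steps.

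**2. Pupils still at risk.** 1 − 0.32 = 68%. At the rate for pupils eligible for free school meals, 1 − 0.46 = 54%.

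**3. What the yes/no term already does.** Assume 32% positive at baseline and 44% of controls positive at 3 years (the Background's figures for ages 12 and 15, used as a proxy), with an 8-point reduction.

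- Mean outcome rate (0.44 + 0.36)/2 = 0.40; variance 0.40 × 0.60 = 0.240.
- New-caries risk in pupils negative at baseline (0.40 − 0.32)/0.68 = 0.118; remaining variance 0.68 × 0.118 × 0.882 = 0.071.

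The yes/no term therefore removes about 71% of the outcome variance (64–71% across baseline rates of 20–46%). A further score among the caries-free, with an assumed odds ratio of 1.5 to 3 per standard deviation, removes another 1.5–14% of what is left.

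**4. Gain among pupils at risk.** Assumptions: 5040 × 0.8 = 4032 followed up, of whom 4032 × 0.68 = 2742 are at risk; control risk (44 − 32)/68 = 17.6%; conditional treatment odds ratio 0.7. An ordinary logistic model is fitted to the expected data with and without the extra predictor. Gain = (z with/z without)² − 1, where z is the log odds ratio over its standard error. Clustering and the repeated measures are ignored. The documents give no prognostic strengths, so these are assumed:

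| Added to the model | Assumed strength | Gain in effective sample size |
|---|---|---|
| Twice-daily brushing | 20–50% not brushing twice daily, odds ratio 1.3–2.5 | 0.2–3% |
| Brushing, plaque and bleeding as one score | odds ratio about 1.25–1.85 per standard deviation | 0.6–5% |
| Early lesions (ICDAS 1–3) | 30–60% affected, 2–5 times the risk | 2–14% |

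The 14% comes from a fit to all 4032 pupils; restricted to the 2742 at risk, the top of the last range is about 16%.

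**5. Where the gain comes from.** With early lesions in 50% and five times the risk, the log odds ratio goes from −0.327 to −0.357, while its standard error rises from 0.106 to 0.111. Then (0.357/0.111)²/(0.327/0.106)² ≈ 1.09. The estimate grows by more than its standard error does.

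**6. In terms of power.** Multiplying the 880.7 by one plus the gain moves 90.3% to:

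- 90.3–91.1% with brushing;
- 90.4–91.6% with all three;
- 90.8–93.6% with early lesions.

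This only scales the planning formula. It is not a power calculation for the planned model.

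**The case against.** The strongest reply is that nothing here is wrong. Adjusting for baseline outcome status is standard and captures most of the available gain (step 3), and which further covariates to add is partly preference. That stands, and it makes this an improvement and not an error.

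Four further points also stand in part.

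- The largest gain needs ICDAS 1–3 recorded at baseline, and the article does not say that it was. The sentence on clinical measures at baseline concerns plaque and gingivitis. For the predictors that are documented, the gain is at most a few per cent.
- The threshold of the baseline term is not stated. Cut at ICDAS 1–6, it would vary among pupils free of dentine caries. ICDAS 4–6 is the natural reading because it matches the outcome, but the point depends on it.
- The calculation is not for the planned model. Pupil and school random effects already stand in for unmeasured differences, so the coefficients in step 5 cannot be carried over, and no stable figure is available for the random-effects version.
- The predictors are not thrown away. Brushing, plaque and bleeding serve the secondary analyses, and the behaviour items on diet, dental services and fluoride are kept for assessing confounding. They are absent from the primary model only.

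None of this gives a reason to leave out a prespecified predictor already in hand.

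**Conclusion.** The point holds as a small efficiency gain forgone. If the baseline term is cut at ICDAS 4–6, the fixed covariate list gives the model no disease information among the 54–68% of pupils who can still develop the outcome, and it uses none of the baseline brushing, plaque or bleeding data. The cost is about 0.2–5% of effective sample size for documented predictors and 2–14% if early lesions are available. These ranges rest on assumed prognostic strengths and an unclustered model.

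A reader might infer more, and the documents do not support it:

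- **Bias.** Randomisation protects the comparison. The smaller unadjusted log odds ratio is a different conditional quantity, and chance imbalance is already reflected in its standard error.
- **A larger standard error.** In these fits, leaving the predictors out makes it slightly smaller.
- **An underpowered trial.** The 40 schools reproduce at 90.3% power with no covariate gain.
- **A fault in the brushing model.** Its covariates are not listed, which is ordinary detail for an analysis plan.

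**What to change.** Before any 2- or 3-year outcome data are seen:

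- State the threshold of the baseline caries term.
- Add baseline twice-daily brushing as a fixed effect in the primary model and, if wished, baseline plaque or gingival bleeding.
- If the baseline examination recorded ICDAS 1–3, replace the yes/no term with three levels: sound; ICDAS 1–3 only; D4–6MFT present.
- Keep the currently stated model as a sensitivity analysis.
- Set a rule for missing baseline values.

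The cost is wording and a few extra parameters in a model with about 4000 pupils. No new data are needed for the documented predictors, and the sample size does not change.

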#### Study procedure

##### Randomisation

Allocation will take place within schools by randomising schools 1:1 to one of two regimes:11–12-year-old pupils (year 7 in England and Wales/S1 in Scotland) to receive the intervention and 12–13-year-old pupils (year 8 in England and Wales/S2 in Scotland) to act as the control group, or12–13-year-old pupils (year 8 in England and Wales/S2 in Scotland) to receive the intervention and 11–12-year-old pupils (year 7 in England and Wales/S1 in Scotland) to act as the control group

An allocation sequence, stratified by school using blocks of size two [30], will be generated by an independent statistician. This sequence will be retained by the statistician and will not be accessible to other members of the trial research team. Once a school is ready to be randomised, following collection of their baseline data, the year groups within that school will be randomised by assigning their year 7 and year 8 cohorts (in that order) to the next block in the allocation schedule. The research team and schools will then be informed of which year group has been allocated to receive the BRIGHT intervention and which has been assigned to the control arm. Since the statistician performing the allocation and the teams recruiting the schools are completely separate, and the allocation schedule cannot be known to anyone but the statistician in advance of randomisation, allocation concealment is assured.

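### The primary model has no random effect for the randomised unit, the year group within school, so its standard error can be too small and its type I error can exceed 5%

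*Protocol article*

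**What the plan says.** Randomisation (Protocol article): "An allocation sequence, stratified by school using blocks of size two" is generated, and "the year groups within that school will be randomised by assigning their year 7 and year 8 cohorts" to the next block. Each school therefore supplies one intervention and one control year group. The same section also describes this as randomising schools between two regimes, which is the same design in other words. The Sample size section names the unit directly: "since randomisation is taking place at the level of the year group, and not at the school-level".

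Data analysis: the primary analysis is a repeated measures logistic multilevel model for caries at 2 and 3 years, with 3 years as the time point of interest. The fixed part is to "control for presence or absence of caries at baseline, year group, time and an interaction between treatment and time as fixed effect covariates". The random part is: "Pupils and school will be included as random effects (to allow for clustering of data within each pupil (over time) and school". No term for year group within school is listed.

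Sample size: the individually randomised calculation is "powered at 90% (5% two-sided α") and a reduction "from 32% to 24% would require a sample size of 1320". For clustering, "a more conservative ICC of 0.02 has been chosen for this trial", described there as the correlation of outcomes within schools. With 60 pupils per year group, 20% attrition and an allowance for contamination, the stated requirement is 40 schools; 42 are to be recruited.

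**The concern.** In a cluster trial the standard error of the treatment effect has to reflect variation between the units that were allocated. Here there are two such units per school, one in each arm. None of the listed terms captures variation between them:

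- The school intercept describes what the two year groups share. That part cancels when they are compared with each other.
- The pupil intercept handles repeated visits. It treats pupils of the same year group as independent, given school.
- The year-group fixed effect must be the two-level factor year 7 v year 8, because a separate level for each year group in each school would be aliased with treatment. It removes the average cohort difference across schools, not the departure of a particular school's two cohorts from that average.

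If the two cohorts of a school differ for reasons of their own, such as intake, teachers or local delivery of the lesson, that difference enters the treatment estimate but not its standard error. At stake are the width of the primary confidence interval and the error rate of the single confirmatory test.

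**Working it through.** **Inputs.** From the Sample size section: 32% v 24%, two-sided 5%, 90% power, ICC 0.02, 60 pupils per year group (120 per school), 20% attrition (so 60 × 0.8 = 48 analysed per year group), and 27% of controls gaining half the benefit. Assumed, because the article does not give it: how the 0.02 divides between school and year group within school.

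**1. Individually randomised size.** Pooled-variance formula for two proportions, per arm:

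n = [1.96·√(2·0.28·0.72) + 1.2816·√(0.32·0.68 + 0.24·0.76)]² / 0.08² = 660, total 1320. This agrees with the article.

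**2. Contamination.** The control rate becomes 0.32 − 0.27 × 0.5 × 0.08 = 0.3092. The same formula for 30.92% v 24% gives 873 per arm, total 1746.

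**3. Number of schools.**

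- Cluster = year group of 60: design effect 1 + (60 − 1) × 0.02 = 2.18. Then 1746 × 2.18 = 3806; / 0.8 = 4758; / 120 = 39.65, so 40 schools. This agrees with the article.
- Cluster = school, 96 analysed pupils, no contamination allowance: 1320 × [1 + 95 × 0.02 = 2.90] / 0.8 / 120 = 39.88, also 40. This leaves out an allowance that the article says is included; with it, the same route gives 1746 × 2.90 / 0.8 / 120 = 52.7.
- All correlation shared by the two year groups of a school, as the primary model implies: the factor for a within-school contrast is 1 − 0.02 = 0.98, and 1746 × 0.98 / 0.8 / 120 = 17.8, so 18 schools.

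The route that uses every stated ingredient and returns 40 is the first one, which applies the ICC to the year group.

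**4. Effect on the type I error.** Let ρ be the part of the ICC at year-group-within-school level, with total 0.02 and m = 48. In units of the total variance:

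- true variance of a year-group mean, given school: ρ + 0.98/m
- variance implied by a school-only model: [0.98 + ρ·m/(2m − 1)]/m
- R = ratio of the first to the second; type I error = 2[1 − Φ(1.96/√R)]

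Example at ρ = 0.02: 0.02 + 0.98/48 = 0.0404; [0.98 + 0.02 × 48/95]/48 = 0.0206; R = 1.96; √R = 1.40; type I error 16.2%.

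| ρ | R | true SE / model SE | type I error, formula | simulated |
|---|---|---|---|---|
| 0 | 1.00 | 1.00 | 5.0% | 5.3% |
| 0.002 | 1.10 | 1.05 | 6.1% | 6.2% |
| 0.005 | 1.24 | 1.11 | 7.9% | 8.0% |
| 0.010 | 1.48 | 1.22 | 10.7% | 9.1% |
| 0.015 | 1.72 | 1.31 | 13.5% | 12.9% |
| 0.020 | 1.96 | 1.40 | 16.2% | 16.4% |

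The simulation used 2000 trials per row, 40 schools × 2 year groups × 48 pupils, a binary outcome with no treatment effect, and a logistic model with school, year and treatment. It had one time point, school as a fixed factor and no baseline covariate, so it approximates the full repeated-measures model. The simulated value at 0.010 lies somewhat below the formula, so about 9% to 11% is a fair reading of that row. In the same data, comparing the school-level year-group differences between the two regimes (t with 38 degrees of freedom) rejected in 4.0% to 5.6% of trials in every row.

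**5. Power once the clustering is allowed for.** At 40 schools, 40 × 120 × 0.8 = 3840 pupils are analysed; 3840 / 2.18 = 1761, against 1746 required. Power is 90.3%. With the design effect on analysed pupils, 1 + 47 × 0.02 = 1.94, it is 93.2%.

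**The case against.** The strongest reply is that the harm is conditional. It requires variation between the year groups of a school beyond the average cohort effect, and the article reports no figure for that. Its ICC of 0.02 is introduced as a within-school correlation. To place all of it at year-group level is to assume that adjacent years of the same school have nothing else in common. The primary model also adjusts for baseline caries, and an outcome that counts treated and untreated disease will be strongly tied to baseline status, so the relevant year-group component may be smaller than any unadjusted value. All of this stands. A reader might infer that the test certainly exceeds 5%, or that its error rate is 16%; the article supports neither statement.

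A second reply is that the 40 schools does not prove what the planners believed. A school-level calculation also reaches 40, and applying 2.18 per year group could be a deliberately cautious shortcut that ignores the within-school pairing. This stands in part. The school-level route works only without the contamination allowance, so the year-group route is the better match, but it is not the only arithmetic possible.

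A third is that a condensed article leaves detail to the full protocol or the statistical analysis plan. That disposes of a wider reading in which the models for the secondary outcomes and the economic evaluation are also faulted: for those the article is silent on cluster terms, and silence here is no error. It does not dispose of the primary model, whose random effects are listed together with their purpose.

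**Conclusion.** The point holds for the primary model. The article makes the year group within school the randomised unit and then specifies random effects that leave it out, while its sample size is best explained by a design effect on that same unit.

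The consequence is a confidence interval that can be too narrow and a type I error between 5% (year-group component zero) and about 16% (the whole 0.02 at year-group level). At a quarter of the planning ICC (0.005) it is about 8%. At the upper end the model's standard error is about 29% too small (1 − 1/1.40). These figures assume 48 analysed pupils per year group, equal cluster sizes, a total ICC of 0.02 and no reduction from baseline adjustment. The omission and the direction of its effect are certain; the size depends on a split that the article does not give.

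**What to change.** In the primary model, add a random effect for year group within school (equivalently, a random school-by-treatment effect), keep the school and pupil effects, and base the degrees of freedom on the number of schools with a small-sample correction. In the sample size text, say that the ICC of 0.02 is applied to the year group.

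The cost is a line or two of wording and slightly wider intervals. If the year-group component proves close to zero, the extra term changes little. No further data or schools are needed, because the planned 40 schools already give about 90% power with this clustering allowed for.
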